### Description of the intervention

#### Facility-based model

This model implements a “passive” approach to the screening and management of household contacts (see definition in the “Study population” section) at the facility level as per current practice. Implementation follows current National Tuberculosis Program (NTP) recommendations, except that a 3-month regimen of daily rifampicin-isoniazid (3RH) as a fixed-dose combination (FDC) is offered as TPT to eligible child contacts. In the context of the study, sites also benefit from additional data collection and trainings with follow-up support for the facility staff.

When a person is diagnosed with bacteriologically confirmed pulmonary TB (index case), the facility staff in charge of TB (TB focal person) asks the index case to bring all household contacts with TB-related symptoms, all young (< 5 years) child contacts or older (5–14 years) child contacts living with HIV or exposed to HIV, irrespective of symptoms, to the health facility for evaluation for TB disease or for eligibility for TPT. This facility-based model is currently implemented in district hospitals in Cameroon for child contacts under 5 years old, but poorly applied for child contacts 5–14 living with HIV. In Uganda, the NTP allows household contact tracing when feasible but evaluation, TPT initiation, and follow-up are required to be done at the facility. In practice, due to lack of transport, the household contact tracing was poorly implemented. In both countries, at facility, TB investigations include clinical examination, sample collection for smear microscopy or Xpert MTB/RIF testing, and CXR when available and indicated, i.e., Xpert is negative or not done. Any contact diagnosed with TB is commenced on TB treatment, registered, and provided with treatment support and follow-up as per NTP guidelines. All sites are supported by the CaP TB program reducing the risk of heterogeneity of diagnosis and treatment of pediatric TB between sites and the two countries. Asymptomatic children who are eligible to receive TPT as 3RH (or 6H if drug-drug interactions with antiretroviral therapy preclude the use of rifampicin) are initiated at the facility with monthly follow-up (Fig. 1). The schedule of the facility-based model is presented in Table 2.

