#### Community-based model

The intervention model is a decentralized, “active” approach to the screening and management of household contacts and is community-based. When an index case is diagnosed with bacteriologically confirmed pulmonary TB, the TB focal person asks whether s/he has child contacts in the household, and if so, then asks whether s/he is willing to receive a team in his/her household for contact symptom screening. If they agree, then an appointment is made and a team comprising a trained community health worker (CHW) and a research assistant goes in the household to screen all contacts (children and adults). If the index case does not have contact children in their household, then s/he is not included in the study, but contact investigation is done under routine care by the TB focal person. During the contact screening visit, the contacts who present symptoms of TB are referred to the health facility for TB investigations. Those who are asymptomatic and eligible for TPT (i.e., < 5 years irrespective of HIV status or 5–14 years and living with HIV) receive another visit by the TB focal person or TB nurse to initiate 3RH (or 6H if drug-drug interactions with antiretroviral therapy preclude the use of rifampicin). The follow-up is done at the household by the CHW after 1 week, 2 weeks, and then monthly in order to rapidly identify the children who develop TB symptoms in the community. The CHW collects the TPT at the health facility before each household visit and brings the remaining pills and documents back to the facility after the visit. During the follow-up visits, the CHW repeats the TB symptom screening, assesses the child’s TPT tolerability and adherence, and assesses the presence of any critical sign. If the child presents critical danger signs, tolerability problems, or TB symptoms, s/he is immediately referred to the health facility for a clinician to consult them (Fig. 2). The schedule of the community-based model is presented in Table 2.

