### Statistical analysis

#### Primary analysis

The denominator for the analysis of the primary endpoint is the number of child contacts < 5 years and HIV-infected 5–14 years declared by the index case at the facility during the inclusion visit. Since discrepancies can be expected between what is declared by the index case and what is observed during contact screening, a sensitivity analysis will be performed using as denominator the number of children < 5 years of age and HIV-infected children of 5–14 years of age identified during the screening. An additional sensitivity analysis will be performed including only participants that followed all study procedures (per-protocol approach) among the declared and then enrolled child contacts. Dropping out of the cascade of cares and potentially being lost to follow-up can be the consequence of the models of care under evaluation. Therefore, lost to follow-up will be kept in the primary outcome analysis. They will be removed from the sensitivity per-protocol analysis.

A generalized linear mixed model with a binomial distribution and logit link function will be used to perform individual-level analysis adjusting for clustering. The regression model will include the fixed effect of treatment assignation and country and one random-effect for the cluster. A degree-of-freedom correction will be applied (between-within method) to deal with the type I error inflation due to the small number of clusters. The primary analysis will focus on the difference between the two study arms adjusted for country, and a secondary analysis will add an adjustment for unbalanced factors (urban/rural, district size) identified in the baseline assessment. For the analysis of the secondary outcomes, a similar mixed model will be used with the same random effects and correction method, focusing on each endpoint of the cascade of care for initiation and completion of TPT and each endpoint of the cascade of care for TB detection. The same model will be applied for the sensitivity analyses.

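### The sensitivity analysis restricted to children identified at screening conditions on a step that differs by arm, so it can understate, erase or reverse a benefit of the community model

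*Protocol article*

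**What the plan says.** In the Protocol article, Primary analysis, the primary denominator is the children under 5, or HIV-infected and aged 5–14, who are "declared by the index case at the facility during the inclusion visit". That count is taken before any screening. The section then notes that "discrepancies can be expected between what is declared by the index case and what is observed during contact screening", and for that reason "a sensitivity analysis will be performed using as denominator the number of children" meeting the same criteria who are "identified during the screening". The mixed model of the primary analysis is to be used for the sensitivity analyses too, so this is a formal between-arm comparison.

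The same section explains why losses stay in the primary analysis: "Dropping out of the cascade of cares and potentially being lost to follow-up can be the consequence of the models of care under evaluation".

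The two arms reach screening by different routes. Under Facility-based model, the TB focal person "asks the index case to bring all household contacts with TB-related symptoms, all young (< 5 years) child contacts" and older children living with or exposed to HIV, to the facility. Under Community-based model, once the index case has agreed, a team "goes in the household to screen all contacts (children and adults". Table 1 lists the proportion of declared children who are screened as a secondary endpoint.

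**The concern.** A declared child in the facility arm who is never brought in is not normally identified at any screening, and so leaves this denominator. The corresponding child in the community arm stays in it if the home visit takes place. Failure to attend is one of the losses the community model is meant to prevent, and the protocol treats the screened share as an outcome in its own right. Restricting the comparison to screened children therefore conditions on a result of allocation. That is the step the section avoids in the primary analysis when it keeps cascade losses.

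Two things are at stake. First, if fewer declared children are screened in the facility arm, the contrast is biased against the intervention, and a prespecified check could appear to contradict a real benefit. Second, a gap between this result and the primary one could not be read as evidence about mis-declaration, because non-attendance would produce a gap as well.

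**Working it through.** **Inputs.** From Sample size calculation: 60% completion in the facility arm, a 10-point difference (so 70% in the community arm), 1500 declared eligible children, ICC 0.01 and cluster-size coefficient of variation 0.50. From the Abstract: 20 clusters, 1:1. The screened shares of declared children, sF (facility) and sC (community), are not in the documents. They are assumptions, shown over a range.

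**1. The plan's own figure.** Mean cluster size is 1500/20 = 75. The design effect is 1 + ((1 + 0.50²) × 75 − 1) × 0.01 = 1.9275. The effective number per arm is 750/1.9275 = 389.1. A two-sided test at 0.05 (the printed 0.05% is read as 0.05; sidedness is not stated) of 60% versus 70% then has 83.4% power by the pooled normal approximation, against 85% stated. That is close enough to take 60% and 70% as rates among declared children.

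**2. Effect of the changed denominator.** Suppose there are no undeclared children. Every completer was screened, so the numerator is unchanged and each rate becomes (rate among declared)/(share screened):

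- difference = 0.70/sC − 0.60/sF
- ratio of proportions = (0.70/0.60) × (sF/sC)

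On the ratio scale, the true effect is multiplied by sF/sC.

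**3. Results with sC = 0.95 (assumed); community rate 0.70/0.95 = 73.7%.**

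| sF (assumed) | Facility rate 0.60/sF | Difference (points) |
|---|---|---|
| 0.95 | 63.2% | +10.5 |
| 0.90 | 66.7% | +7.0 |
| 0.80 | 75.0% | −1.3 |
| 0.75 | 80.0% | −6.3 |
| 0.70 | 85.7% | −12.0 |

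The first row shows that equal screening does little harm: dividing both rates by 0.95 only stretches the difference slightly.

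**4. Break-even.** The difference is below zero when sF/sC < 0.60/0.70 = 0.857. That means sF below 0.77, 0.81 or 0.86 for sC = 0.90, 0.95 or 1.00.

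**5. What break-even means.** The quantity p/s is completion among screened children. Reversal is therefore the same event as screened community children completing less often than screened facility children. At break-even the two are equal, the whole 10 points comes from more children being screened, and the sensitivity contrast is exactly zero.

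**6. Size against sampling error (sF = 0.70, sC = 0.95).** The denominators are 525 and 712.5. The design effects, with mean cluster sizes 52.5 and 71.25, are 1.646 and 1.881. The standard error is √(0.857 × 0.143 × 1.646/525 + 0.737 × 0.263 × 1.881/712.5) ≈ 0.030, so z ≈ −0.120/0.030 ≈ −4.0. At sF = 0.75, z ≈ −2.0; at sF = 0.80, z ≈ −0.4.

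**7. Denominator that keeps never-screened children.** With no undeclared children, the contrast is 60% versus 70% whatever sF and sC are. If home visits add undeclared children equal to 10% of those declared, the community rate lies between 0.70/1.10 = 63.6% (none of them completes) and 70.0% (they complete at 70%). With 20% added, the lower end is 0.70/1.20 = 58.3%.

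**The case against.** The strongest reply is that the primary analysis is already protected: its denominator is fixed before screening and it retains losses. The disputed text is a labelled sensitivity analysis that changes no sample size or decision rule. The screened share is reported as a secondary endpoint, so a divergent result could be traced to screening uptake. Using observed children also has a legitimate reason: HIV status at ages 5–14 may be unknown until testing is offered (Symptom screening), so declaration alone cannot fully settle eligibility. All of this stands and limits the severity. None of it shows that the screened-only contrast separates mis-declaration from non-attendance.

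A reader might infer that the analysis will turn a true benefit into apparent harm. The documents do not support that. They give no screened shares, and reversal needs screened community children to complete less often than screened facility children. The Background expects household follow-up to improve completion. Selective attendance by motivated families could produce a reversal, but nothing in the protocol quantifies it.

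A reader might also infer that the community arm keeps nearly all its children. The home visit needs the index case's agreement and contacts must consent, so losses occur there too. In Uganda the national programme allows household contact tracing when feasible, although the article says it was poorly implemented in practice. The loss is mainly, not only, in the facility arm.

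Finally, the article condenses a full protocol, and an analysis plan may exist. Either could define the term so that unscreened children are kept. The point concerns the denominator that the article states.

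**Conclusion.** The point holds as a should-fix. The stated sensitivity denominator depends on a post-randomization step that the arms carry out differently, and it conflicts with the section's own reasoning about cascade losses. If a smaller share of declared children is screened in the facility arm, the ratio of completion proportions shrinks by the factor sF/sC. In points, the plan's +10 becomes anything from +7.0 to −12.0 over facility shares of 90% to 70% with 95% screened at home. Those shares are assumptions, as is the absence of undeclared children. Reversal below a ratio of 0.857 is possible, not certain.

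Two further readings go beyond the text. One is that this is the principal robustness check: the section names two sensitivity analyses and a covariate-adjusted secondary analysis without ranking them. The other is that its purpose is to test whether unblinded declaration differs by arm: the section says only that declared and observed children may differ. The primary result is not affected.

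**What to change.** Define the sensitivity denominator identically in both arms: every eligible child declared by the index case, plus any further eligible child found at screening. Count declared children who were never screened as non-completers. Report completion among screened children by arm as a descriptive cascade step, without a between-arm test.

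The cost is a change of wording made before analysis, using data already collected. The downside is that undeclared children will be found mainly by home visits, so ascertainment of the added children still differs by arm, and step 7 of the working shows this can matter if many are added and few complete. Report the number of added children by arm next to the declared-only primary result so that readers can judge it.

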Cascade of care for TB detection of adult contacts	Number of adults screened and proportion of adults screened among household identified adult contacts
	Proportion of adults with symptoms suggestive of TB: presumptive TB cases
	Proportion of adults presumptive TB cases diagnosed with TB
Safety and treatment adherence for children under TPT	Proportion of children with serious adverse events
	Proportion of children with adverse events of interest: peripheral neuropathy, clinical hepatotoxicity
	Ratio of dose taken as indicated (ticked) on the treatment card by the parent/guardian over the total number of doses to be taken by prescription
Endpoints at 6 months	Treatment outcomes of children started on TB treatment
	Proportion of children diagnosed with TB after initiation of TPT: during and after TPT
	Proportion of children diagnosed with TB among those who were not started on TPT and were not diagnosed with TB at baseline assessment
Before-after comparison for TB adult and pediatric cases and for TPT initiation and completion from health facility registers	Number of patients diagnosed with TB and registered
	Proportion of children among all patients diagnosed with TB and registered
	TB treatment outcomes of patients (adults and children) diagnosed with TB and registered
	Number of children started on TPT
	Completion rate of children started on TPT
Acceptability and feasibility of the intervention	Attitudes, willingness, and motivation to have a visit in their household
	Myths, anticipated fears, stigma, and risks of having a visit in their household
	Actual experiences with household visits
	Perception of the disease, its risk, and the notion of prevention, including TPT
	Description of critical events during house visits and how these were dealt with
	Identification of main constraints
Fidelity of the study	Proportion of delivered activities compared to the intended activities of the model
Cost-effectiveness of the intervention	Costs of CHW/community nurse assessment and treatment
	Costs of facility-based assessment and treatment
	Other facility costs (overheads, diagnosis, hospitalizations)
	Direct parent/guardian costs (related to care)
	Indirect parent/guardian costs (unrelated to care, e.g., dissaving, travel costs)

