### Study design

This is a two-arm parallel cluster randomized study comparing two models of care for TB contact investigation and management. This study contains three phases:
Baseline phase (phase I) in which retrospective data collection and register quality checks were done in order to assess if the facility registers could be a reliable source of documents for the study. During this phase, there was also a baseline qualitative assessment with adult TB patients who are parents and stakeholders to better prepare the intervention phase and assess the acceptability and feasibility of the proposed activities.Intervention phase (phase II) includes implementation and participant recruitment in the two models of care and study data collection.Explanatory phase (phase III) contains the endpoint analysis and reporting, a cost-effectiveness analysis, and a post-intervention qualitative assessment with adult TB patients who are parents and cluster stakeholders to collect the acceptability of the implemented package.

This research is known under the name of CONTACT study (Community Intervention for Tuberculosis Active Contact Tracing and Preventive Therapy) and represents a research project embedded in a multi-country pediatric TB implementation program called Catalyzing Pediatric TB Innovations (CaP TB) led by the Elizabeth Glaser Pediatric AIDS Foundation (EGPAF) and funded by Unitaid.

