The proportion of children notified in the facility TPT register among all notified cases during the intervention period will be compared between the two models of care and will also be compared with the same proportions before intervention for the same time period (data collected during the baseline assessment). The proportion of confirmed TB among all pediatric notified cases and the proportion of treatment completion will also be compared between the two models and with the pre-intervention period.

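### Pre-intervention register data on preventive therapy, a cluster-level proxy for the primary outcome, enter no stated between-arm model, which gives up a modest amount of efficiency in a 20-cluster trial

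*Protocol article*

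**What the plan says.** The primary analysis is a logit mixed model: "The regression model will include the fixed effect of treatment assignation and country and one random-effect for the cluster". For small-sample inference, "A degree-of-freedom correction will be applied (between-within method) to deal with the type I error inflation due to the small number of clusters". Beyond that, "a secondary analysis will add an adjustment for unbalanced factors (urban/rural, district size) identified in the baseline assessment". The sensitivity analyses and the cascade endpoints use the same kind of model.

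Under Study design, the protocol describes a "Baseline phase (phase I) in which retrospective data collection and register quality checks were done". Table 1 lists register-based before-after endpoints, among them the number of children started on TPT and the "Completion rate of children started on TPT". The last paragraph of the Primary analysis section takes the share of children in the facility TPT register among all notified cases, compares it between the two models of care, and adds that it "will also be compared with the same proportions before intervention for the same time period (data collected during the baseline assessment"). That is the only stated use of the pre-intervention TPT data.

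**The concern.** A cluster's earlier record of starting and completing TPT is a natural candidate to predict how it performs in the trial. The randomisation balanced country and the previous year's count of confirmed cases. It did not balance TPT practice, so chance imbalance on past practice is possible with ten clusters per arm. Under the protocol's own inputs, about half the variance of the treatment effect lies between clusters, and the number of clusters cannot be raised (Limitations). A cluster-level covariate that absorbs part of that variance would raise power with no extra children or clusters. The protocol collects candidate data, states its models explicitly, and leaves these data out of all of them. What is at stake is precision, not validity.

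**Working it through.** **Inputs from Sample size calculation:** 60% against 70%; 1500 children; ICC 0.01; coefficient of variation (CV) of cluster size 0.5, and up to 0.7. There are 20 clusters randomised 1:1, so m = 1500/20 = 75 children per cluster and 750 per arm. A two-sided 5% level is assumed. The printed alpha of 0.05% would give about 29% power, so 5% was evidently used.

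**The protocol's own figure.** Design effect = 1 + [(1 + CV²)m − 1] × ICC = 1 + (1.25 × 75 − 1) × 0.01 = 1.9275. The effective size is 750/1.9275 ≈ 389 per arm. A normal-approximation test of two proportions then has 83.4% power, close to the stated 85%. At CV 0.7 it is 80.0%, which matches the stated floor.

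**With the planned correction.** Between-within degrees of freedom are taken as 20 clusters − 3 fixed parameters (intercept, arm, country) = 17. SE = √[(0.24 + 0.21)/750 × 1.9275] = 0.0340. Noncentrality = 0.10/0.0340 = 2.94. Power from the noncentral t is 79.1% (75.5% at CV 0.7).

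**Adding one cluster covariate.** Let r be its cluster-level correlation with the outcome. On a linear-scale approximation the between-cluster part shrinks by (1 − r²):

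Design effect = (1 + CV²) × m × ICC × (1 − r²) + (1 − ICC) = 0.9375 × (1 − r²) + 0.99, with 16 degrees of freedom.

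| r (assumed) | Design effect | Power, CV 0.5 | Change from 79.1% (points) |
|---|---|---|---|
| 0 | 1.93 | 78.8% | −0.3 |
| 0.3 | 1.84 | 80.6% | +1.5 |
| 0.4 | 1.78 | 82.0% | +2.8 |
| 0.5 | 1.69 | 83.8% | +4.6 |
| 0.7 | 1.47 | 88.5% | +9.4 |

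At CV 0.7 the changes at r = 0.3, 0.5 and 0.7 are +1.7, +5.4 and +11.1 points.

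**How large can r be?** Sampling noise in the baseline measure caps it. If the baseline ICC is also 0.01 (assumed) and n children per cluster are observed, reliability R = 0.01/(0.01 + 1/n), and r cannot exceed √R.

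- *Completion among children started.* The protocol cites 15% to 24% initiation and requires at least 50 index cases per year. With one eligible child per index case and 50 to 75 index cases, n runs from 50 × 0.15 = 7.5 to 75 × 0.24 = 18. So r is at most 0.26 to 0.39, and the gain at most about 1 to 3 points.
- *Children starting and completing per estimated eligible child.* With n = 50 to 100 (assumed), r is at most 0.58 to 0.71. That ceiling requires a perfect true correlation between periods and error-free registers. With a true correlation of 0.7 (assumed), r is 0.7 × 0.58 = 0.40 to 0.7 × 0.71 = 0.49, and the gain is 2.9 to 4.5 points. With 0.5, r is 0.29 to 0.35 and the gain 1.3 to 2.1 points.

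**The case against.** The strongest reply is that the plan is sound as it stands. It adjusts for the stratification factor, corrects for few clusters, and gives an unbiased comparison. On this view the covariate is an optional extra resting on an undocumented correlation, and several facts argue for a weak one.

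- A reader might infer that phase I yields a baseline value of the primary outcome. The documents do not support that. The primary denominator is "the number of child contacts < 5 years and HIV-infected 5–14 years declared by the index case at the facility during the inclusion visit", whereas the registers are described as giving children started and completion among those started. Dividing by registered cases is a construction, and the protocol does not say that children in the TPT register are limited to contacts of confirmed index cases.
- Conditions changed. National guidance was six months of isoniazid, while the trial offers a three-month regimen in both arms with training and study-supplied drugs. In the community arm, care moves to the household, so past facility performance may predict less there.
- Register quality was itself in question: phase I was run so that "retrospective data collection and register quality checks were done in order to assess if the facility registers could be a reliable source". Limitations reports inconsistencies at some sites, and Challenges says that one Cameroon cluster was replaced.
- A reader might infer that covariate adjustment is the only route to more power. It is not: other cluster covariates, including the two already planned for the secondary model, could also absorb between-cluster variance.

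All of this stands, and it lowers the expected gain. It does not show a cost beyond one degree of freedom, and noise in a measurement taken from before the intervention does not bias a randomised comparison. The last paragraph of the Primary analysis section already defines a similar TPT ratio, so the covariate is close to something the protocol intends to compute.

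**Conclusion.** The point holds as a missed efficiency option, not an error. Register data that give a cluster-level proxy for the primary outcome are collected, and no stated between-arm model uses them. A realistic gain is about 1 to 5 power points from a base of about 79%, against a loss of 0.3 points if the covariate is useless.

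This rests on the protocol's sample-size inputs, 17 and 16 degrees of freedom, a linear-scale approximation to the logit model, and an assumed r of about 0.3 to 0.5. Gains of 7 to 11 points, which a reader might infer from r of 0.6 to 0.7, sit near or at the noise ceiling and should not be expected. Nor is the gap between 79% and the stated 85% caused by omitting the covariate: it comes mainly from applying the planned correction to the power calculation.

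**What to change.** Before any comparison of outcomes by arm, add to the Primary analysis section one cluster-level fixed effect in the primary mixed model: pre-intervention TPT performance from the phase I registers over one fixed period. An example is children starting or completing TPT per registered case, in line with the ratio already defined for the before-after comparison. State a single scale that allows zeros (linear or rank). A log scale fails for a cluster with no completers, which is plausible at 15% to 24% initiation. Make its use conditional on the phase I register check confirming that the measure is available for all 20 clusters, including the replaced one. Keep the country-only model as a sensitivity analysis.

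The statistical cost is one degree of freedom (17 to 16) and the chance that a noisy covariate brings little. No new data collection should be needed if the availability check passes. Because the trial is open-label, enrolment began in October 2019 and investigators follow the data on a dashboard, the change should be dated and the absence of any prior by-arm comparison documented.
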